### Intervention

Participants allocated to the intervention group will receive the 8-week PEP delivered during scheduled physical education sessions, consisting of one 50-minute session per week. To ensure feasibility within the school setting and minimize disruption to academic activities, sessions will be conducted during scheduled physical education periods. Each session will involve approximately 15 to 20 students and will be supervised by a trained educator to ensure correct exercise performance, safety, and adherence to the intervention protocol. Both groups will receive sessions of equal frequency and duration (one 50-minute session per week); however, only the intervention group will receive structured posture education content. The program includes postural awareness training, core strengthening exercises, ergonomic correction strategies, guided movement activities, and breathing and relaxation techniques. Participants’ baseline posture control, and core endurance will be assessed during the initial session to guide appropriate exercise starting levels. All participants will begin with low-intensity posture-focused activation exercises to ensure familiarization with correct movement techniques.

Progressive overload will be applied throughout the intervention by gradually increasing exercise hold duration, number of repetitions, sets, and movement complexity in accordance with established physical activity and exercise guidelines [13]. Functional postural control tasks and coordinated movement patterns will be introduced in the later blocks to enhance transfer of learning to daily activities. Exercise modifications will be provided based on individual tolerance and performance to ensure safe and standardized participation. Participant progression will be monitored weekly using standardized educator observation checklists to document exercise performance quality, tolerance, and adherence to the program. To facilitate gradual adaptation and skill acquisition, the PEP is delivered in four progressive blocks across the 8-week intervention period. The structure and progression of intervention components across these blocks are summarized in Table 1. Each PEP session will follow a standardized 50-minute structure consisting of postural awareness activities, core strengthening exercises, ergonomic correction practice, guided movement activities, and breathing and relaxation exercises. Exercises will include abdominal bracing, pelvic tilts, scapular setting, chin tuck exercises, wall alignment drills, bridge exercises, modified plank holds, bird-dog progression activities, thoracic mobility exercises, and functional posture-control tasks. Initial intensity will emphasize correct movement technique, controlled breathing, posture awareness, and low-intensity activation exercises. Progression across the intervention blocks will occur through gradual increases in exercise hold duration, repetitions, sets, movement complexity, coordination demands, and reduction in verbal cueing. Detailed exercise descriptions, session progression parameters, and FITT-based exercise implementation details are provided in Supplementary File 1 to enhance reproducibility and methodological transparency Table 2.

**Table 1 tbl0001:** Block-wise progression of the PEP.

Session Component	Duration (minutes)	Block 1 (Weeks 1–2)	Block 2 (Weeks 3–4)	Block 3 (Weeks 5–6)	Block 4 (Weeks 7–8)
Postural awareness training	10	Technique learning	Posture correction	Self-monitoring skills	Habit integration
Core strengthening exercises	15	Static activation	Endurance progression	Dynamic control	Functional stability
Ergonomic correction strategies	5	Ergonomic education	Practice and feedback	Behaviour application	Independent management
Guided movement activities	15	Mobility training	Alignment control	Coordination tasks	Functional movement
Breathing and relaxation techniques	5	Basic breathing	Posture-linked breathing	Movement integration	Self-regulation

Note: Total session duration = 50 minutes. The PEP is delivered once per week for 8 weeks during scheduled physical education sessions.

**Table 2 tbl0002:** Mapping of the ADDIE framework to the development and implementation of the PEP.

ADDIE phase	Application in the PEP
Analysis	Identification of adolescent postural risks, sedentary behaviour, ergonomic needs, and school-based feasibility requirements through literature review, school-context evaluation, and preliminary needs assessment to guide intervention planning.
Design	Development of intervention objectives, session structure, progression blocks, and outcome domains through expert-informed planning, evidence-based exercise selection, and Delphi content validation procedures.
Development	Preparation of educational materials, exercise components, observation checklists, and assessment procedures
Implementation	Delivery of one 50-minute PEP session weekly for 8 weeks during scheduled physical education sessions
Evaluation	Delphi content validation, pilot feasibility testing, fidelity monitoring, and outcome assessment at baseline, Week 4, and Week 8

### Description of intervention phases

#### Block 1 (Weeks 1–2): technique learning and familiarization

During the initial block, participants will focus on technique learning and familiarization with correct postural alignment. Activities include basic postural awareness exercises, static core activation (e.g., abdominal bracing and scapular setting), ergonomic education on sitting and standing posture, and simple mobility exercises. Breathing techniques emphasize diaphragmatic breathing to promote relaxation and postural control.

#### Block 2 (Weeks 3–4): posture correction and endurance development

In this block, participants will engage in posture correction exercises with increased focus on maintaining alignment during sustained positions. Core strengthening exercises progress to endurance-based tasks, with longer hold durations and increased repetitions. Ergonomic strategies are reinforced through practice and feedback, and guided movement activities target alignment control during functional movements. Breathing is integrated with posture correction tasks.

#### Block 3 (Weeks 5–6): dynamic control and coordination

This block introduces dynamic control and coordination tasks. Participants perform exercises requiring maintenance of postural alignment during movement, including coordinated movement patterns and functional tasks. Core exercises progress to dynamic control activities, and participants begin applying ergonomic principles in simulated daily activities. Movement–breathing integration is emphasized.

#### Block 4 (Weeks 7–8): functional integration and self-management

In the final block, participants focus on functional integration and independent self-management of posture. Exercises incorporate functional stability tasks and real-life movement patterns. Participants are encouraged to self-monitor posture and apply ergonomic strategies independently. Breathing and relaxation techniques support self-regulation and long-term adherence to correct postural behaviors.

Exercise progression across blocks is guided by participants’ baseline posture control and core endurance assessed during the initial session. Intensity and complexity increase gradually with longer hold durations, higher repetitions, greater coordination demands, and functional posture tasks. Weekly educator observation checklists are used to monitor performance quality, tolerance, and adherence, and exercise modifications are provided when necessary. Detailed examples of session structure, exercise progression, and instructional components are provided in Supplementary File 1.

Participants in the control group will continue their usual academic curriculum and attend the standard school physical education (PE) program, consisting of one 50-minute session per week. Trained PE teachers conduct the PE sessions and typically include general warm-up exercises, team sports activities such as football or basketball, basic fitness exercises including running and stretching, and recreational movement tasks. The sessions are designed to promote general physical fitness and participation rather than structured posture training or targeted core stabilization exercises. No specific posture education or ergonomic training components will be delivered to the control group during the study period.

### Outcome measures

Standardized outcome assessments will be conducted at baseline (Week 0), mid-intervention (Week 4), and post-intervention (Week 8). All assessments will be performed at approximately the same time of day to minimize physiological variability.

Primary outcome measures include lung function, postural alignment, and functional aerobic capacity. Postural alignment will be assessed using standardized posture grid analysis based on validated observational criteria [9,10]. Participants will stand in a standardized anatomical position in front of a calibrated posture grid, and alignment will be evaluated relative to vertical and horizontal reference lines to identify deviations in head position, shoulder symmetry, and spinal curvature. Posture grid assessment has demonstrated acceptable inter-rater and intra-rater reliability in previous adolescent posture assessment studies [9,10]. Standardized assessor training and assessment procedures will be implemented to support consistency during data collection.

Functional aerobic capacity will be assessed using the six-minute walk test (6MWT) conducted according to established guidelines [14]. Participants will be instructed to walk as far as possible along a standardized corridor for six minutes with consistent verbal encouragement. The total distance covered in meters will be recorded as the outcome measure. In addition to walking distance, participants’ heart rate, blood pressure, and oxygen saturation (SpO₂) will be measured before, during, and after the test. Perceived exertion will be assessed using Borg’s Rating of Perceived Exertion (RPE) scale, a validated tool used to measure subjective exercise intensity during physical activity [15]. The 6MWT has demonstrated good reliability and validity for assessing submaximal exercise capacity in adolescent populations [8,16]. Changes in walking distance will be interpreted alongside baseline performance and age-appropriate normative reference values derived from healthy children and adolescents [17].

Lung function will be evaluated using peak expiratory flow rate (PEFR) measured with a calibrated peak flow meter [18,4]. Participants will perform three maximal expiratory efforts from a standing position following standardized instructions, and the highest recorded value (L/min) will be used for analysis. PEFR is a widely accepted indicator of ventilatory capacity and pulmonary function in adolescent respiratory assessment. PEFR values will be interpreted with consideration of participant age, sex, and anthropometric characteristics where appropriate. Because PEFR is effort-dependent, standardized instructions, demonstration procedures, and repeated trials will be used to improve measurement consistency. PEFR values will be interpreted using age- and sex-appropriate normative reference values where available [18,4]. Although universally established MCID values for PEFR in healthy adolescent populations remain limited, changes in PEFR will be interpreted alongside baseline performance and repeated assessment trends. PEFR measurement has demonstrated acceptable validity and test–retest reliability in adolescent respiratory assessment when standardized instructions and repeated trials are applied [18,4].

Secondary outcome measures include resting cardiovascular parameters, physical activity level, psychological well-being, and ergonomic knowledge and behaviour. Resting blood pressure and heart rate will be measured using a validated automatic digital monitor following standardized procedures [5]. Physical activity level will be assessed using the International Physical Activity Questionnaire Short Form (IPAQ-SF), which evaluates time spent in walking, moderate-intensity activity, vigorous-intensity activity, and sedentary behaviour over the previous seven days [19]. It has been shown to be valid and reliable across multiple populations [19]. Psychological well-being will be assessed using the General Health Questionnaire-28 (GHQ-28), a self-report screening instrument comprising four domains, including somatic symptoms, anxiety and insomnia, social dysfunction, and depression [20]. The GHQ-28 has demonstrated good reliability and validity across different populations [20]. Knowledge, attitude, and practice related to ergonomic behaviour will be evaluated using a validated adolescent-adapted questionnaire assessing posture awareness, ergonomic practices, and behavioural habits in educational settings [21,22].

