## Abstract

Adolescents are increasingly exposed to sedentary behaviours and poor ergonomic environments that may adversely affect posture, aerobic capacity, and psychological well-being. This article describes a standardized protocol for implementing and evaluating an 8-week Posture Education Program (PEP) among high school students aged 14–17 years using a randomized controlled trial design. The intervention includes postural awareness, core strengthening, ergonomic correction, guided movement, and reflective behavioural activities delivered during physical education sessions. The control group will continue standard physical education without posture-specific training. The program was developed using the ADDIE instructional framework, while the International Classification of Functioning, Disability and Health framework guided outcome selection. Primary outcomes include postural alignment, aerobic capacity, and lung function. Secondary outcomes include physical activity, psychological well-being, and ergonomic knowledge and behaviour. This protocol provides a reproducible framework for school-based posture education interventions and integrates multidimensional assessment of postural, cardiorespiratory, behavioural, and psychological outcomes within a school-based adolescent population.

Structured 8-week school-based posture education intervention integrated into physical education sessions.

Multidimensional assessment of posture, aerobic capacity, lung function, and psychological well-being.

Reproducible randomized controlled trial protocol guided by ADDIE and ICF frameworks.

Specifications table

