### Sample size calculation

Sample size was calculated using G*Power version 3.1 for a mixed-design repeated-measures ANOVA examining the group × time interaction. Peak expiratory flow rate (PEFR) was selected as the primary outcome for sample size estimation. The selection of the effect size was informed by a previous randomized controlled trial investigating the effect of McKenzie exercises on pulmonary function among individuals with forward head posture, which demonstrated significant improvements in PEFR following the intervention [12]. To avoid overestimating the intervention effect and to ensure a conservative estimate for the present school-based posture education programme, a medium effect size (f = 0.25), alpha level of 0.05, and statistical power of 0.80 were used for the sample size calculation. The analysis indicated that a minimum of 28 participants per group was required. Allowing for an anticipated attrition rate of 20%, the target sample size was increased to 35 participants per group, resulting in a total planned sample of 70 students.

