### Data analysis

Data will be analyzed using IBM SPSS Statistics version 29.0 (IBM Corp., Armonk, NY, USA). Baseline characteristics will be summarized using descriptive statistics, including mean and standard deviation for continuous variables and frequencies and percentages for categorical variables. The primary analysis will follow the intention-to-treat (ITT) principle, whereby all randomized participants will be analyzed according to their originally allocated groups regardless of intervention adherence or withdrawal where possible. The ITT approach was selected to preserve the benefits of randomization, minimize attrition-related bias, and provide a pragmatic estimate of intervention effectiveness within a real-world school-based setting.

Missing data patterns will be examined, and the extent and reasons for missing data will be reported. Missing outcome data will be handled using appropriate imputation procedures, where necessary, to facilitate the inclusion of all randomized participants in the primary analysis, consistent with recommended approaches for randomized controlled trial analysis [23].

A mixed-design repeated-measures ANOVA will be used to examine group (intervention vs control) × time (baseline, mid-intervention [Week 4], and post-intervention [Week 8]) interaction effects for primary and secondary outcomes. Assumptions of normality, homogeneity of variance, and sphericity will be assessed using appropriate diagnostic procedures. Where the assumption of sphericity is violated, Greenhouse–Geisser correction will be applied. Significant interaction effects will be explored using post hoc pairwise comparisons with adjustment for multiple comparisons. Effect sizes for repeated-measures ANOVA will be reported using partial eta squared (η²p), while Cohen’s d will be calculated for post hoc pairwise comparisons, consistent with commonly recommended effect size reporting practices for intervention studies [12]. Statistical significance will be set at p < 0.05.

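### Three unranked primary outcomes are each tested at p < 0.05 with no error control across them, while the trial is sized on PEFR alone at an undivided alpha of 0.05

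*Protocol article*

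**What the plan says.** Outcome measures lists three primaries: "Primary outcome measures include lung function, postural alignment, and functional aerobic capacity". The Abstract gives the same three in another order: "Primary outcomes include postural alignment, aerobic capacity, and lung function". Neither place ranks them or singles one out.

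Sample size calculation works from one outcome: "Peak expiratory flow rate (PEFR) was selected as the primary outcome for sample size estimation". Its inputs are "a medium effect size (f = 0.25), alpha level of 0.05, and statistical power of 0.80 were used for the sample size calculation", and its result is given as "The analysis indicated that a minimum of 28 participants per group was required". The alpha is not divided.

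Data analysis applies one mixed-design repeated-measures ANOVA to examine "interaction effects for primary and secondary outcomes". It sets a single threshold: "Statistical significance will be set at p < 0.05". On multiplicity it says: "Significant interaction effects will be explored using post hoc pairwise comparisons with adjustment for multiple comparisons". That adjustment starts only after an interaction is already significant, and it acts within that outcome. The article states no requirement that all three succeed, no testing order and no split of alpha.

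**The concern.** The parts of the article do not fit together. A sizing alpha of 0.05 fits one primary test, but three primary tests are declared, each judged at the full 0.05. The adjustment that is described comes after the point where the error accumulates, so it does not protect a claim made across the three outcomes.

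At stake is what a positive trial would mean. Suppose PEFR misses 0.05 and six-minute walk distance reaches it. From the plan, a reader could not tell whether the trial had succeeded on its primary objective, and the significant outcome would not be the one the trial was sized on. That cannot be settled credibly once results are known.

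**Working it through.** **Inputs from the article.** Three primary outcomes (Abstract; Outcome measures). Threshold 0.05 for each (Data analysis). f = 0.25, alpha 0.05, power 0.80, 28 per group or 56 in total, and 35 per group after 20% attrition (Sample size calculation). Two groups and three time points.

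**Assumed, because the article does not give them.** The between-outcome correlation r, the repeated-measures correlation rho, the sphericity epsilon (taken as 1), and a rule that any one significant primary counts as success.

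**Step 1: the plan's own figure.** For a group × time interaction with k = 2 groups and m = 3 times, power follows a noncentral F with λ = f²·N·m·ε/(1 − ρ), df1 = (k − 1)(m − 1)ε and df2 = (N − k)(m − 1)ε. For 80% power at alpha 0.05 with ε = 1:

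| rho | total N needed | power at N = 56 |
|---|---|---|
| 0 | 54 | 0.824 |
| 0.3 | 38 | 0.938 |
| 0.5 | 28 | 0.987 |

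The stated 28 per group is approached at rho = 0 (27 per group). Without rho and epsilon it can be neither confirmed nor refuted. The attrition step reproduces: 28/0.8 = 35. The sizing therefore provides for one test at 0.05.

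**Step 2: error across three tests with no true effect.** If the tests are independent, 1 − 0.95³ = 1 − 0.857375 = 0.1426. The Bonferroni bound is 3 × 0.05 = 0.15, whatever the correlation. Three correlated interaction F-tests were simulated with 35 per group and 20,000 replicates:

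| r | chance that at least one p < 0.05 |
|---|---|
| 0 | 13.9% (exact 14.3%) |
| 0.2 | 14.1% |
| 0.3 | 13.8% |
| 0.5 | 12.6% |
| 0.7 | 11.0% |
| 0.9 | 8.5% |

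The rejection rate for a single outcome stayed at 4.9% to 5.2%, so the excess comes from having three chances. Relative to 5%, the inflation is 8.5/5 = 1.7-fold to 14.3/5 = 2.9-fold.

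**Step 3: power if error is controlled.** Holm compares the smallest of the three p-values with 0.05/3 = 0.0167, the next with 0.025 and the last with 0.05. The first step is the strictest. With f = 0.25, N = 56, ε = 1, df1 = 2 and df2 = 108:

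| rho | λ = 0.0625 × 56 × 3/(1 − ρ) | power at 0.05 | power at 0.0167 | total N for 80% at 0.0167 | per group after 20% attrition |
|---|---|---|---|---|---|
| 0 | 10.5 | 0.82 | 0.69 | 70 | 44 |
| 0.3 | 15.0 | 0.94 | 0.86 | 50 | 32 |
| 0.5 | 21.0 | 0.99 | 0.96 | 36 | 23 |

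The planned 35 per group covers the strictest step at rho = 0.3 or 0.5, but not at rho = 0.

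**The case against.** **The rate is conditional.** The article describes tests and a threshold, not a success rule. If all three outcomes had to be significant, or if each were reported as its own question, there would be no any-of-three inflation. This stands. It is why the result is a range under a stated condition, and why a flat claim of about 14%, or of three times the nominal level, would go too far: that is the independent case. No all-must-succeed rule is stated either, so the any-of-three reading remains open.

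**The SAP may settle it.** Rules across outcomes are often written there. However, this article itself fixes the threshold, the tests and the place where adjustment applies. An SAP that controlled the primary family would have to add to or change that scheme. The number and ranking of primary outcomes is a protocol-level decision.

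**The trial is described as preliminary.** Study design does use that word, but it also gives effectiveness as an aim. The point bears on how heavily the defect weighs; it does not remove it.

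**Sizing on one of several primaries is common.** True. Calling PEFR primary for the purpose of sizing does not by itself contradict the list of three. The difficulty is the undivided alpha combined with three uncontrolled tests.

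**A reader might count five primary tests**, because the posture grid looks at the head, the shoulders and the spine. The article says what is observed. It does not say that three posture variables are tested separately, and scoring detail may sit in the full protocol. No error rate is claimed on that basis.

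**Conclusion.** The concern holds in conditional form. The stated scheme leaves the three primary tests without error control, and the alpha used for sizing fits only one of them. With no true effect on any outcome, and success claimable on any one, the false-positive rate is about 8.5% (r = 0.9) to 14.3% (r = 0) instead of 5%. For three tests it cannot exceed 15%. The between-outcome correlation and the success rule are assumptions.

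A reader might also infer that a correction would cost almost nothing because power stays at 0.96. That figure needs a repeated-measures correlation of 0.5, which the article does not state. Under the same formula, 0.5 gives a required total of 28, not 28 per group. At rho = 0, which comes close to the stated 56, power at 0.0167 is 0.69. The cost has to be shown as a range.

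**What to change.** Choose one of two options before any outcome data are seen.

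1. **Keep three primaries.** State in Data analysis that Holm is applied across the three primary group × time interaction tests at a familywise 0.05, with postural alignment represented by one prespecified score. Restate the power at the strictest step, with the assumed repeated-measures correlation and epsilon written out. No new measurements are needed. Power for one outcome with 56 completers is 0.69 to 0.96 over the correlations shown. At the low end, holding 80% would need 44 per group instead of 35.
2. **Name one primary outcome** in Outcome measures and the Abstract, and make the other two secondary. PEFR fits the existing sizing, so alpha and sample size stay as they are. Which outcome should lead is the investigators' choice. If it is not PEFR, the sample-size justification must be rewritten for the outcome chosen.

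Either option takes one or two sentences in the text, plus the restated power under the first.

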**Table utbl0001:** 

**Subject area**	Medicine and Dentistry
**More specific subject area**	School-based physiotherapy / adolescent posture intervention
**Name of your method**	Posture Education Program (PEP) for High School Students
**Name and reference of original method**	Developed using the ADDIE instructional design model and informed by ergonomic and posture education literature.
**Resource availability**	Peak flow meter, automatic blood pressure monitor, posture grid, IPAQ-SF, GHQ-28, KAP questionnaire, stopwatch, standardized 6-minute walk test (6MWT) track setup, and intervention session materials.

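### Blood pressure is scheduled during the six-minute walk, whose distance is a primary outcome; a mid-walk cuff reading would probably add avoidable noise to that distance and shorten it

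*Protocol article*

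**What the plan says.** All of this is in the protocol article.

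- **Status of the outcome.** Under Outcome measures: "Primary outcome measures include lung function, postural alignment, and functional aerobic capacity". Aerobic capacity is measured by the six-minute walk test at baseline, Week 4 and Week 8.
- **What is recorded.** "The total distance covered in meters will be recorded as the outcome measure".
- **How the walk is done.** "Participants will be instructed to walk as far as possible along a standardized corridor for six minutes with consistent verbal encouragement". The test is said to follow a cited guideline.
- **What is measured around it.** Heart rate is listed together with "blood pressure, and oxygen saturation (SpO₂) will be measured before, during, and after the test".
- **Equipment.** The resource row of the Specifications table begins "Peak flow meter, automatic blood pressure monitor, posture grid". For the separate secondary outcome, the text says "Resting blood pressure and heart rate will be measured using a validated automatic digital monitor following standardized procedures".
- **How distance will be read.** Changes are to be interpreted alongside baseline performance and "age-appropriate normative reference values derived from healthy children and adolescents".

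The article does not say how a blood pressure reading is obtained from a walking student, how many are taken, whether the clock is stopped, or how lost time is treated.

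**The concern.** The test has a fixed duration and its result is a distance, so each second spent not walking at full effort comes straight off the outcome. An automatic cuff monitor ordinarily needs the arm to be still while it reads. This is practical knowledge rather than document text, but nothing in the article removes the difficulty. An assessor who follows the sentence literally must slow or halt the student, or accept a doubtful reading.

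Three things would follow if the walk is disturbed:

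1. Time lost to a reading depends on the cuff, on errors and on repeats, not on fitness. It would vary from visit to visit in the same student and so enter the within-student error.
2. Distances would tend to be shorter than the student could achieve.
3. A pause is also a rest, which could alter the heart rate and perceived exertion recorded with the test.

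No stated benefit is set against this. The cardiovascular secondary outcome is resting blood pressure and heart rate, and the Safety and adverse events section attaches no rule to a reading taken during the walk.

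**Working it through.** The plan gives no figure on this point, so there is none to reproduce. The check is a comparison of the statements, then an illustration of size.

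**The statements side by side.** The distance instruction asks for maximal distance in a fixed time. The measurement sentence places blood pressure inside that time. Both are affirmative statements in the same paragraph, so the point does not rest on an omission.

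**Size of the loss.** From the document: test time is 6 × 60 = 360 s. Assumed: one reading costs a full standing pause of 15 to 60 s, and the student would otherwise walk 600 m.

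Share lost = pause / 360. Distance lost = 600 × pause / 360.

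| Pause (assumed) | Share of 360 s | Loss at an assumed 600 m |
|---|---|---|
| 15 s | 4.2% | 25 m |
| 30 s | 8.3% | 50 m |
| 45 s | 12.5% | 75 m |
| 60 s | 16.7% | 100 m |

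The loss is smaller if the student only slows, and larger with more than one reading.

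**Noise.** A constant loss does little harm to a group × time comparison; a varying one does. Walking speed is 600/360 = 1.667 m/s. If pauses were spread evenly over a range of width w, their standard deviation (SD) would be w/√12.

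- 20 to 45 s: 25/√12 = 7.2 s, or 12.0 m.
- 15 to 60 s: 45/√12 = 13.0 s, or 21.7 m.

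Against an assumed between-student SD of 60 m at one visit:

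- √(60² + 12.0²) = 61.2 m, a rise of 2%.
- √(60² + 21.7²) = 63.8 m, a rise of 6%.

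The interaction, however, is judged against within-student variation. The SD of a change between two visits is 60 × √(2(1 − r)), where r is the correlation between visits (assumed). Pauses that are independent between visits add √2 × 12.0 = 17.0 m or √2 × 21.7 = 30.6 m.

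| r (assumed) | SD of change, no pause | Pauses 20–45 s | Pauses 15–60 s |
|---|---|---|---|
| 0.5 | 60.0 m | 62.4 m (+4%) | 67.4 m (+12%) |
| 0.7 | 46.5 m | 49.5 m (+6%) | 55.7 m (+20%) |

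So the added noise runs from slight to appreciable, depending on inputs that the documents do not give.

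**The case against.** The strongest reply is that the article nowhere says the walk is interrupted. One timing phrase covers three signs, and it may be a condensed list in which only heart rate and oxygen saturation are meant during the walk. The test is tied to a guideline, and the article reports a pilot after which assessment logistics were refined. The equipment list is also incomplete: it omits an oximeter and the exertion scale, both of which the text uses, so a device suited to walking may exist.

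Much of this stands. The interruption is an inference, the device argument is not conclusive, and the size is entirely assumed. What does not stand is that this is merely missing detail. The sentence expressly includes blood pressure among the measurements during the test. The guideline is not at hand, so it settles the matter for neither side. The pilot shows that the measures could be administered and were acceptable, not that distance was undisturbed.

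A reader might go further in two ways, and the documents support neither:

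- **That the treatment comparison is biased.** Both arms have the same assessments at the same visits, assessors are blinded, and the analysis tests group × time. A roughly constant loss largely cancels there, and nothing shows that pauses would differ by arm.
- **That comparison with the norms is invalid.** This holds only if the reference values came from uninterrupted walks, which cannot be checked here. The article also reads changes, in which a constant loss largely cancels.

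**Conclusion.** The point holds as a minor, easily mended flaw. The article schedules blood pressure inside a timed walk whose distance is a primary outcome, and the only blood pressure device it names is an automatic monitor. A literal reading would probably slow or pause the student, add avoidable within-student noise and shorten the distance.

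The size rests on assumptions: 4% to 17% of the test time for one standing pause of 15 to 60 s, or about 25 to 100 m at 600 m, and less if the student only slows. These figures are shortfalls in an individual distance, not errors in the treatment effect. It would be too strong to say that the primary outcome is corrupted, since the text states no interruption.

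**What to change.** Amend the sentence under Outcome measures so that blood pressure is taken before and after the walk only. Keep heart rate and oxygen saturation during the walk only if a worn sensor records them without the student stopping. State that the procedure is identical at baseline, Week 4 and Week 8 and in both arms.

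If a mid-walk blood pressure is wanted for a reason that the article does not give, it should state that reason, name the device and say how the reading is obtained without interrupting the timed distance.

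The cost is one edited sentence and one reading fewer per test, which saves assessor time. The only loss is the mid-walk blood pressure; the planned secondary outcome of resting blood pressure and heart rate is unaffected.
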